### Interventions

#### Cardiorespiratory Exercise Intervention

This intervention will be a 12-week progressive and individualized exercise program with a frequency of 3 sessions per week and a session duration of 60 minutes (total: 36 exercise sessions). The intervention is designed to alleviate symptoms of dyspnea, improve functional capacity, and relieve mental health problems in the short term. A further aim is to preserve physical function while improving health-related QoL in the long term. As recommended by the Official American Thoracic Society/European Respiratory Society Statement [20], 12 education sessions (30 minutes per session) will be included in and delivered together with the first exercise session in each week to motivate and empower the patients to form regular exercise habits and improve health [21,22]. A steering group will be formed to design the exercise intervention, develop relevant documentation, and monitor the implementation. Group members will include exercise experts, public health specialists, occupational therapists, doctors, and other stakeholders. Textbox 1 and Table 1 provide a summary of the intervention.

This program will be delivered using a home-based tele-exercise approach to reduce the potential to infect other individuals [24], reduce health care burden and costs for both health care providers and patients, and improve participation and retention of rehabilitation [25]. Some evidence, although not for COVID-19, has suggested that home-based pulmonary rehabilitation with minimal exercise equipment is effective and may be a viable alternative to equipment-intensive clinic-based programs [18,26]. Other studies concluded that the web-based tele-exercise approaches were as effective as conventional face-to-face interventions [27] and could enhance the reach and engagement of the rehabilitation process [21,25]. We will build and develop a web-based platform in our International Rehabilitation Network Center for Patients With COVID-19 to deliver the intervention.

Description of the cardiorespiratory exercise intervention (educational session).
**Educational session**
Each session will last 30 minutes and will be held before the first exercise session of each week, for a total of 12 sessions.The sessions will be developed mainly based on social psychological theories of intentional behavior and motivation, and aimed to improve motivation, self-regulation, and habit-formation relating to exercise [20,22,23].Our team members published a similar theory-based behavior change intervention in 2020 [22]. In brief, in each session, the patients will be asked about their exercise and other types of physical activity (PA), related theoretical determinants (eg, self-efficacy), and other related factors (eg, social and environmental factors). They will then receive personally tailored feedback incorporating effective behavioral change techniques (eg, goal setting) to promote motivation, solve problems, make action plans, prevent relapse, enhance self-regulation, and form healthy habits. A recap of the previous session will be added starting in the second session. Pictures, graphs, and videos will also be used where needed.

**Table 1 table1:** Description of the cardiorespiratory exercise intervention (exercise session).

Content	Description
Exercise session	3 sessions per week for a total of 36 sessions; session duration will gradually increase from 40 to 60 minutes. Initial face-to-face briefing will be given to enhance compliance and ensure that the patients can exercise properly. Video feedback will be provided during each session.
Warm-up	Warm-up will last 5-8 minutes, including both static stretching and dynamic stretching.
Aerobic training	There will be no requirement of intensity in the initial sessions (1-2 weeks). Exercise intensity will start from Rating 3 of the Borg Category-Ratio 0-10 Scale (Borg Dyspnea Scale) and progressively increase to Rating 6. The training mode will be interval training in the first 4-6 weeks, followed by continuous training. The duration will gradually increase from 10 to 30 minutes. Effective exercises will be selected after a thorough review of the existing literature, such as walking, high knees, butt kicks, and stepping.
Resistance training	The intensity will be one that evokes local muscular exhaustion in 6 to 12 repetitions (ie, a 6-12 repetition maximum) for major muscle groups; workload will increase when an individual can perform the current workload for 1 or 2 more repetitions than the required number in two consecutive exercise sessions [23]; there will be no requirement of intensity in the initial sessions (1-2 weeks). The volume will be 2-4 sets, 8-12 repetitions, with 1-minute rest intervals (approximately 10 minutes). A resistance band will be used to strengthen the muscles of either upper or lower extremities alternatively in each session. Effective exercises will be selected after a thorough review of existing literature. Exercise examples include band bicep curl (arms), band lateral pull (arms), lateral band walk (legs), and seated banded leg extensions (legs).
Cool-down	Cool-down will last 5-8 minutes, including static stretching and dynamic stretching.
Inspiratory muscle training	The device used will be a POWERbreathe Classic (IMT Technologies Ltd). The volume and intensity will be 30 breaths at 50% of maximal inspiratory pressure (approximately 5-8 minutes). The increment of intensity will be 5% load increase each week. Additional Inspiratory muscle training sessions will be performed without supervision according to a suggested frequency of twice daily. Maximal inspiratory pressure will be measured with a portable hand-held mouth respiratory pressure meter (MicroRPM, CareFusion Micro Medical).

#### Structure of the Exercise Intervention

The intervention will include the following components: (1) a set of home-based tele-exercise sessions during which remote monitoring of vital signs will be required; (2) an individualized action plan to perform various daily physical activities; (3) educational sessions on self-management and habit formation; (4) access to a call center; (5) counselling sessions to enhance motivation to regularly engage in daily physical activities. The counseling intervention will be facilitated via a remote patient monitoring system. Patients will be equipped with an activity monitor (Mi Band 5, Xiaomi Corporation) that connects to a customized smartphone or tablet with a global system for mobile communication (GSM) connection that will receive, display, and send the data via the internet to a secure web-based server at the university. Patients will receive real-time feedback on the smartphone or tablet about their physical activity levels and their daily adjusted physical activity goals. A teleconference between the patient and the counselor will also be possible via the smartphone or tablet (using Zoom) in order to continually enhance adherence and goal achievement. Patients’ daily physical activities will be acquired by the Mi Band 5 via Bluetooth technology to the smartphone or tablet; from the smartphone or tablet, data will be sent to the central server. Following the completion of the intervention, all patients will receive detailed individual feedback in relation to the outcome measures obtained via a meeting with the research team. This will comprise a question and answer session with relevant experts in their field of expertise. Patients will also receive a detailed personalized report with recommendations and information relating to the outcomes of the intervention.

The content of the exercise intervention will be developed with reference to the Official American Thoracic Society/European Respiratory Society Statement published in 2013 [20]. Each exercise session (40-60 minutes) will include a warm-up, aerobic training, resistance training, a cool-down, and inspiratory muscle training (IMT) [20,28,29]. Aerobic exercise will be arranged before resistance training, as recent evidence has shown that this order produces greater benefits than performing resistance training first [30]. Additional IMT sessions will be performed without supervision according to a suggested frequency of twice daily [20]. Before the first exercise session of each week, an additional educational session (30 minutes) will be delivered to improve motivation, self-regulation, and habit formation relating to exercise [20]. The contents of the educational sessions will be developed mainly based on social psychological theories of intentional behavior and motivation and effective behavioral change techniques (Textbox 1) [20,22]. All patients will be briefed face-to-face initially to ensure that they can undertake the intervention properly and to enhance their compliance with the intervention. In addition, they will be videotaped during the exercise sessions, and real-time feedback will be given via the internet.

Aerobic exercise intensity will be determined using the Borg Category-Ratio 0-10 Scale (Borg CR10 Scale) modified for dyspnea, as recommended by the American College of Sports Medicine guidelines for patients with pulmonary diseases [23]. The exercise intensity will start from Rating 3 (equivalent to 53% peak work rate, ie, moderate intensity) in the first 2-4 weeks and progressively increase to Rating 6 (equivalent to 80% peak work rate, ie, vigorous intensity). Exercise intensity and session duration will be adjusted according to each patient’s response and tolerance. Lighter intensities than Rating 3 may be adopted when there is a need (eg, for those with severe conditions). Patients will be given specific and standardized instructions on the ratings in advance. A pulse oximeter (Beurer PO 40, Beurer GmbH) will be used to monitor oxygen saturation in the initial exercise sessions to avoid exercise-induced oxyhemoglobin desaturation. In terms of intensity of resistance training, a practical approach to determine the appropriate intensity will be adopted, in which workloads will be set at levels that evoke local muscular exhaustion in 6 to 12 repetitions, as the one repetition maximum approach may overestimate or underestimate the optimal resistance for individuals [20,31]. Progressive target goals and detailed training plans will be set up together with each patient based on their physiological measurement results [21].

The exercise intervention will be delivered and supervised by experienced instructors. We will recruit persons who have been educated in either exercise science or rehabilitation. Each exercise session will be facilitated by two instructors dedicated to a group of 5-7 patients through the web-based platform in our International Rehabilitation Network Center for Patients With COVID-19. They will also be responsible for monitoring developments and training during the intervention.

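### Training oximetry is stated only for the initial sessions, although its purpose is to avoid exercise-induced desaturation and the load is raised later; tie it also to the steps up in load

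*Protocol article*

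**What the plan says.** Under Structure of the Exercise Intervention, the protocol article names a pulse oximeter that "will be used to monitor oxygen saturation in the initial exercise sessions to avoid exercise-induced oxyhemoglobin desaturation". It gives no number of sessions or weeks for this.

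The same section starts aerobic work at Rating 3 of the Borg scale, equated with 53% of peak work rate, for the first 2-4 weeks. The intensity will then "progressively increase to Rating 6 (equivalent to 80% peak work rate, ie, vigorous intensity"). Two sentences allow individual handling: "Exercise intensity and session duration will be adjusted according to each" patient's response and tolerance, and "Lighter intensities than Rating 3 may be adopted when there is a need".

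Table 1 (aerobic training) adds: "There will be no requirement of intensity in the initial sessions (1-2 weeks"). The resistance-training row has the same allowance. On mode it says "The training mode will be interval training in the first 4-6 weeks, followed by continuous training", and on aerobic time "The duration will gradually increase from 10 to 30 minutes". There are 3 sessions a week, 36 in all.

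The list of components in the same section requires remote monitoring of vital signs in the home tele-exercise sessions, without naming the signs and without a time limit.

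**The concern.** The article fixes both the timing and the purpose of training oximetry, and the timing serves the purpose poorly. Readings are stated for the start of the programme, where Table 1 sets no intensity requirement, and not for the later sessions in which intensity, bout length and mode are all stepped up.

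Participants are enrolled because FVC or diffusing capacity is below 90% of predicted, and they train at home. As written, a patient can move to a higher rating or to continuous training without a stated saturation reading in training at that load. What is at stake is participant safety only.

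**Working it through.** **Inputs.** From Table 1: 3 sessions a week, 36 in total; no intensity requirement in the initial 1-2 weeks; interval training for 4-6 weeks, then continuous; aerobic time 10 to 30 minutes. From Structure of the Exercise Intervention: Rating 3 (53% of peak work rate) in the first 2-4 weeks, rising to Rating 6 (80%). From Sample Size Calculation: 43 patients per group, 20% dropout.

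**Plan's own count.** 3 sessions × 12 weeks = 36, as stated.

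**Sessions with stated oximetry.** If initial spans *k* weeks, 3*k* sessions are covered and 36 − 3*k* are not. The article does not give *k* for oximetry, so two readings are tried:

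| Assumed meaning of initial | Covered | None stated |
|---|---|---|
| 1-2 weeks (Table 1 usage) | 3 to 6 | 33 to 30 |
| 2-4 weeks (Rating 3 phase) | 6 to 12 | 30 to 24 |

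Combined range without stated oximetry: 24/36 = 67% to 33/36 = 92%.

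**Where the higher load falls.**
- Interval training takes 3 × 4 = 12 to 3 × 6 = 18 sessions, so continuous training takes 36 − 18 = 18 to 36 − 12 = 24. Even with *k* = 4, coverage ends at session 12 and continuous training starts at session 13 at the earliest. Neither reading covers a continuous session.
- The target rises by a factor of 80/53 = 1.51 in relative work rate.
- Aerobic time rises from 10 to 30 minutes, a factor of 3.

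**Where else saturation could be read.**
- *Cardiopulmonary exercise test.* SpO2 is monitored continuously during an incremental ergometer test whose results guide prescription (Cardiopulmonary Exercise). The Borg scale is used in the same test (Dyspnea). Measurements are at baseline and weeks 13 and 25 (Outcomes). Each patient's rating and saturation are therefore seen across rising work rates before training starts, but in the laboratory and not within the 12-week home programme.
- *Remote vital signs.* SpO2 is neither included nor excluded.
- *Safety Observations.* The vital signs listed there omit SpO2, but the list is for follow-up visits and does not settle what is monitored in training.
- *Supervision.* Two instructors watch 5-7 patients over the internet. No saturation reading is stated as part of this.

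No section states a saturation reading in home training at the point where load is raised.

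**The case against.** The strongest reply is that the sequence is coherent as it stands. The baseline exercise test already shows how saturation behaves as the Borg rating climbs, training plans are built on physiological results, intensity is set by dyspnea rather than by an imposed load, progression follows tolerance, sessions are supervised live, and a physician screens for contraindications. Remote vital-sign monitoring may already include SpO2. Finally, a steering group that includes doctors will design the programme and its documentation, and a journal article need not say which session carries which sensor.

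Much of this stands, and it narrows the point. A reader might infer that patients train at vigorous intensity unmonitored, or that their saturation at such work rates has never been seen. The documents support neither. Nor does the follow-up-visit list show that SpO2 is left out of the home sessions. Reaching 80% of peak work rate is a target for those who tolerate it, not a load forced on everyone.

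The argument from condensation does not remove the point, because the article states the timing and does not leave it open. The exercise test is incremental laboratory ergometry, while training is walking, high knees, butt kicks and stepping at home, in bouts that lengthen to 30 minutes. The plan itself adds an oximeter to Borg ratings at the start, so it does not treat the laboratory test and symptoms as sufficient then. If SpO2 is among the remote vital signs throughout, limiting the oximeter to the initial sessions needs reconciling with that, and the gap is one of wording only.

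**Conclusion.** The point holds in a limited form: the article states no saturation reading for home training when load is raised, although avoiding desaturation is the stated reason for the oximeter. On two assumed meanings of initial, 24 to 33 of 36 sessions (67-92%) have no stated oximetry, including all 18 to 24 continuous sessions.

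Those percentages should not be read as a measure of danger. They count sessions under an assumption; the article gives no desaturation rate, so the size of the risk is unknown. The two exercise arms have 2 × 43 = 86 randomized patients, about 69 after 20% dropout (86 × 0.8 = 68.8), and not all will reach Rating 6. Efficacy, power and alpha are unaffected. This is a cheap improvement for participant safety.

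**What to change.** In Structure of the Exercise Intervention, state that the named oximeter is used:
- in the initial sessions;
- in the first session at Rating 3, if that comes later;
- in the first session after each increase in the prescribed Borg rating;
- in the first session of continuous training.

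In the component list of the same section, state that SpO2 is among the remotely monitored vital signs in those sessions. Let the doctors on the steering group (Cardiorespiratory Exercise Intervention) set the threshold and the response. No separate trigger for bout length is proposed, because it rises gradually; a first reading at a rating may therefore precede the longest bout at that rating.

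**Cost.** Protocol wording and a longer device loan; the device is already named and the sessions are already supervised. If ratings rise in whole steps, which is an assumption because the article names only Ratings 3 and 6, the additions are Ratings 4, 5 and 6 plus the change of mode: 4 sessions (4/36 = 11%), or 5 (5/36 = 14%) where Rating 3 also comes later. It is fewer for patients who do not reach Rating 6 or whose change of mode coincides with a rating step. Over 86 patients that is 4 × 86 = 344 to 5 × 86 = 430 monitored sessions; after 20% dropout, 4 × 68.8 ≈ 275 to 5 × 68.8 = 344.

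Stated oximetry would then cover 3 + 4 = 7 to 12 + 4 = 16 of 36 sessions. The aim is a reading at each step up in rating and at the change of mode, not in every session.

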### Sample Size Calculation

Aiming to achieve a large effect size of 0.8, based on a meta-analysis of effectiveness of exercise interventions on dyspnea and exercise capacity in patients with pulmonary fibrosis diseases [28], using a significance level of 0.05, power level of 90%, and 20% drop-out rate, a sample size of 172 patients (43 per group) was preliminarily estimated for the study. The meta-analysis result was chosen because there is no similar rehabilitation program available that combines exercise and Chinese herbal medicine. Furthermore, the outcome variables in that meta-analysis are similar to our primary outcomes. Given that the effects of Chinese herbal medicine were not considered, the final sample size will be re-estimated using preliminary outcomes from the pilot study.

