### Statistical Analysis

A generalized linear mixed model will be used to compare between-group differences in changes of outcome variables at the 12- and 24-week periods of the study, where group and time are the two factors of interest. Mediating effects of the gut microbiome and immune function tests will be determined by fitting linear regression models for pulmonary and other outcomes, respectively. A significance level of 0.05 will be adopted (two-tailed test). Intention-to-treat procedures will be applied to the data sets obtained. Missing data will be imputed using multiple imputations with chained equations, except for those from dropouts, which will be imputed with the baseline data. Data will be scrutinized for normal distribution prior to data analysis. Sensitive analyses, such as per-protocol analysis, as-treated analysis, and analysis for complete cases, will only be performed to assess the robustness of the data analyses.

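### Exercise is taught in classes of 5-7 in two of the four arms, but neither the stated model nor the sample size allows for correlation within a class

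*Protocol article*

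**What the plan says.** Patients are randomized individually and equally to four arms (Randomization and Allocation Concealment). Two of the arms receive the exercise programme. Under Structure of the Exercise Intervention, every session is run by "two instructors dedicated to a group of 5-7 patients". Of the same instructors it adds: "They will also be responsible for monitoring developments and training during the intervention". Table 1 sets "3 sessions per week for a total of 36 sessions". The herbal-only arm takes granules at home and the waiting-list arm is untreated, so neither has classes.

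The Statistical Analysis section specifies a generalized linear mixed model "where group and time are the two factors of interest", with a two-sided 5% level. It names no class or instructor effect and does not list the random effects. The Sample Size Calculation uses an effect size of 0.8 and a 5% level, and continues: "power level of 90%, and 20% drop-out rate, a sample size of 172 patients (43 per group". It mentions no design effect. It calls the figure preliminary and plans a re-estimation from pilot data.

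The article does not say whether class membership stays the same over the 12 weeks, or whether combined-arm and exercise-only patients attend the same classes.

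**The concern.** This is a partially nested design: individual randomization, with group delivery in some arms only. Patients who share instructors and classmates over up to 36 sessions may end with more similar outcomes than patients who do not. If so, an exercise-arm mean is less precise than its number of patients suggests. A model without a class term then understates the standard error of exercise versus non-exercise comparisons, rejects too often under the null, and has less real power than stated.

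The lead hypothesis is that the combination does best. One of its key contrasts, combined versus exercise-only, compares two arms that both have classes, so how the classes are composed bears directly on it.

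**Working it through.** **Inputs from the article.** Effect size 0.8 (read as a standardized mean difference), two-sided 5% level, 90% power, 20% dropout, 43 per group, classes of 5-7 (midpoint m = 6).

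**Assumed.** No class ICC is given; the only ICC in the article is the test-retest reliability of the walk test, a different quantity. I use ρ = 0.01, 0.05 and 0.10, with stable classes.

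**1. Reproducing the sample size.** A two-sample t-test with d = 0.8 needs 33.8, so 34 per arm. Then 34/(1 − 0.20) = 42.5, so 43 per arm and 4 × 43 = 172. This matches exactly, under independence. Power at 34 per arm is 90.2%.

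**2. Exercise arm versus non-exercise arm.** Design effect in the exercise arm: DE = 1 + (m − 1)ρ. True over naive variance of the difference: V = (DE + 1)/2. Type I error = 2[1 − Φ(1.96/√V)]. Power comes from the noncentral t with 34 per arm and the variance multiplied by V.

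| ρ | DE | √V | Type I error | Power |
|---|---|---|---|---|
| 0.01 | 1.05 | 1.012 | 5.3% | 89% |
| 0.05 | 1.25 | 1.061 | 6.5% | 87% |
| 0.10 | 1.50 | 1.118 | 8.0% | 83% |

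Over class sizes 5 to 7 the type I error runs from 5.2% (m = 5, ρ = 0.01) to 8.6% (m = 7, ρ = 0.10). A normal approximation gives power about one point higher.

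**3. Allowing for dropout.** With 20% dropout a class of 6 leaves 6 × 0.8 = 4.8 completers.
- ρ = 0.05: DE = 1 + 3.8 × 0.05 = 1.19, V = 1.095, type I error 6.1%.
- ρ = 0.10: DE = 1.38, V = 1.19, type I error 7.2%, power 85%.

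**4. If the two exercise arms share classes, three patients from each.** Exercise-only versus waiting list then has DE = 1 + 2ρ in the exercise arm. V = 1.01, 1.05 and 1.10, and type I error is 5.1%, 5.6% and 6.2%.

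**5. Combined versus exercise-only.**
- Arm-specific classes: V = DE = 1.05, 1.25, 1.50. Type I error 5.6%, 8.0%, 11.0%; power 89%, 83%, 76%. With 4.8 completers per class, type I error is 7.2% at ρ = 0.05 and 9.5% at ρ = 0.10.
- Classes shared equally: the class effect cancels from the difference, so V = 1 − ρ = 0.99, 0.95, 0.90. Type I error 4.9%, 4.4%, 3.9%.

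**6. Simulation check.** 20,000 runs, naive t-test, classes of 6, 36 patients per arm, ρ = 0.05: 6.5% (exercise versus unclustered), 8.2% (arm-specific classes) and 4.6% (shared classes). These agree with the formulas.

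**The case against.** The best reply is that much of the clustering is inferred.

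- **The model.** Group and time are called the factors of interest, the random effects are not listed, and the Outcomes section says further patient variables will be adjusted for. A reader might infer that the model contains only two terms and treats patients as independent; the article does not say so. An analysis plan that is not shown could include a class effect. That stands as a caution. It does not remove the point, because the sample size is stated in this document and reproduces only without a design effect, and a later plan cannot use class membership that nobody recorded.
- **Fixed classes.** A reader might infer the same patients and the same two instructors for all 36 sessions. The text describes how each session is staffed. The word dedicated suggests stability but does not establish it, and changing membership would weaken the clustering.
- **Every exercise comparison.** A reader might infer that all exercise contrasts are anti-conservative, and combined versus exercise-only the most. That holds only if classes are arm-specific, which is not stated. With equally shared classes this contrast is slightly conservative.
- **A small ICC.** "This program will be delivered using a home-based tele-exercise approach", and "Exercise intensity and session duration will be adjusted according to each patient’s response and tolerance". Many outcomes are laboratory or lung function measurements. A low ICC is plausible, and at 0.01 the effect is negligible.
- **Provisional sample size.** The figure is due for re-estimation. That is fair, and it is the natural place to deal with the matter.

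**Conclusion.** The point holds conditionally. What the article establishes is group delivery with shared instructors in two of four individually randomized arms, no class effect in the stated model, and a sample size that assumes independence. What it does not establish is a positive ICC, stable classes, or arm-specific classes.

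Given a positive ICC and reasonably stable classes, exercise versus non-exercise comparisons are anti-conservative if class is left out of the model. The size is modest: with an ICC up to 0.10 and six same-arm patients per class, type I error reaches about 8.0% and power falls to about 83%. Allowing for dropout, the values at ICC 0.10 are about 7.2% and 85%. For combined versus exercise-only, neither direction nor size can be fixed until the class composition is stated. I am confident about the structure and only moderately so about the size. This should be corrected, but it does not undermine the trial.

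**What to change.** - State whether classes keep the same members and instructors, and whether they are arm-specific or shared by the two exercise arms.
- Record class and instructor identifiers for every exercise patient.
- Fit a class random effect for patients in the exercise arms only, treating each non-exercise patient as a cluster of one (partially nested model). If classes are shared, cross class with arm.
- Use Kenward-Roger or Satterthwaite degrees of freedom, since there would be few classes: 43/7 to 43/5, about 6 to 9 per arm if arm-specific.
- In the planned re-estimation, restate the power of each exercise contrast over an assumed ICC range.

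The cost is two variables in the database, one model term, slightly wider confidence intervals for most exercise contrasts and a slightly lower stated power. No extra patients are needed to correct the inference. Restoring 90% power would need more: with equal inflation of both arms, 44, 49 or 54 enrolled per arm at ICC 0.01, 0.05 or 0.10 for exercise versus non-exercise (34 × V rounded up, divided by 0.8 and rounded up). Whether to do that is a separate decision for the re-estimation.
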